### Interventions

Each workplace will have a research workplace leader who will be based on-site for the duration of the study. The workplace leader will collaborate with the workplace stakeholders to co-ordinate the study and monitor daily adherence to the interventions.

#### Nutrition education in workplaces B and C

Nutrition education will include three components group presentations, individual nutrition consultations and detailed nutrition information.

Group presentations will consist of monthly 'lunch and learn’ group nutrition sessions (30 minutes per session) and will be delivered to all employees. These sessions will concentrate on portion control, reading food labels, general healthy eating, and reducing sugar, salt and fat dietary intakes. Sessions will be repeated a number of times per month so that all participants in all shifts have the opportunity to attend. Peer support and group discussion will allow for more effective learning.

Individual dietary counselling (20 minutes per session) with a nutritionist or dietician will be conducted with each participant at baseline, and follow-up sessions held at 3-4 months, 7-9 months and 13-16 months. The nutritionist or dietician will provide advice on how to follow a healthy diet, reach or maintain a healthy BMI and achieve or maintain a healthy resting blood pressure. The individual consultation will be based on the participant’s individual lifestyle, health status results (weight, BMI, waist circumference) and dietary recall assessments. The 'Food Choice at Work’ healthy eating booklet will be offered to each participant at the end of the first consultation. The booklet will support nutritional advice during consultations.

A 'healthy eating chat table’ will be situated outside the canteen during break times twice a month. All employees will have the opportunity to sit and ask a nutritionist or dietician about healthy eating.

Detailed nutrition information will be offered throughout the duration of the intervention using six key methods: (a) posters and leaflets, (b) emails, (c) menu labelling, (d) quizzes, (e) shopping cards, and (f) personalized measurement cards.

Posters and leaflets will be displayed throughout the workplace and based on the theme of the 'lunch and learn’ monthly nutrition sessions. This information will be replaced monthly.

Monthly emails will be disseminated to all employees using the workplace intranet to inform the employees of the scheduled activities for that month.

A unique healthy eating traffic-light coding system will be applied to the daily menus in the employees’ canteens and vending machines on-site. The coding system will display the number of calories and traffic lights will show the amounts of fat, saturated fat, total sugars and salt per portion size of the meal or food item. The traffic lights will also be displayed in words for employees who are colour blind (Figure 3).

**Figure 3 F3:**
[figure not shown]
**Traffic-light display.** The traffic-light coding system will be applied to all food menus in workplaces that will implement the nutrition education intervention. The coding system will display the number of calories and traffic lights will show the amount of fat, saturated fat, total sugars and salt per portion size of the meal or food item. Traffic-light threshold values are guided by the Food Safety Authority of Ireland (FSAI) and the Food and Drug Administration labelling system.

All traffic-light threshold values will be based on the Irish nutrient goals from the Food Safety Authority of Ireland (FSAI) and the Food and Drug Administration labelling system. The Irish nutrient goals have been developed on the basis of a caloric intake of 2000 kilocalorie (kcal) per day [23]. The recommended percentage intake is: for fat, 20% to 35% (<80 g); for saturated fat, <10% (≤20 g); for total sugar, ≤20% (≤90 g); and for salt, ≤6 g [23]. A green light will be applied if the food or meal does not exceed 5% of the recommended percentage intake. An amber light will be applied to a food or meal that contains between 5% and 20% of the recommended percentage intake. A red light will be applied if the food or meal exceeds the limit of 20% of the recommended percentage intake.

Two short quizzes focused on the traffic-light displays and the 'lunch and learn’ group nutrition sessions will be given to all employees each month. Randomly selected winners will receive free lunches.

Pocket-sized food choice shopping cards will be offered after baseline assessments. These cards will provide guidance on how to select healthy food choices when purchasing food at work or outside of work using our own unique traffic-light coding system.

Pocket-sized personal measurement cards (pocket size) will be offered after baseline assessments to allow participants to log and follow their progress throughout the study regarding their health status. Individual dietary advice from the nutrition consultations will also be recorded on the card.

#### Environmental dietary modification in workplaces C and D

The menus in workplaces C and D will be nutritionally analyzed using NetWISP software (Weighed Intake Software Program; Tinuviel Software, Warrington, UK) before the study commences. The workplace stakeholders and the research team will discuss and reach a consensus on all future environmental dietary modifications in the workplace canteens and vending machines. Taste testing will be conducted by the workplace stakeholders and the research team before the implementation of any modifications. All catering staff will be trained before and during the intervention period so there is high compliance with the specific dietary modifications and portion control.

The following five environmental dietary modifications will be recommended: (a) restriction of fat, saturated fat, sugar and salt, (b) increase in fibre, fruit and vegetables, (c) price discounts for whole fresh fruit, (d) strategic positioning of healthier alternatives and (e) portion size control.

For the restriction of fat, saturated fat, sugar and salt, all menus need to be modified. Stock and bouillon should be removed from all recipes and replaced with a recommended low-salt stock. Salt should be eliminated from all cooking processes. Fresh herbs, spices and garlic should be introduced to develop additional flavour. Savoury options that are high in salt, saturated fat and fat should be restricted (for example, sausage rolls, croissants) and replaced with low-fat or low-salt options. High-salt products (gravy mixes, stock cubes) and processed meats (bacon, corned beef) will be reduced and replaced where possible with low-salt options (turkey, chicken, fish). Fresh herbs, spices and garlic will be introduced to develop additional flavour. Ready-made meals will be removed and replaced with freshly cooked options. Full-fat dairy products (that is milk, cream, cheese and butter) will be replaced with low-fat options where possible. Cheese and cream will not be used as a garnish on meals. The amount of cheddar cheese will be reduced in all dishes. Cooking methods with oil, such as deep-fat frying, will be limited and will be replaced with methods of boiling, poaching, grilling, steaming and baking where possible. Only plant oils will be used in cooking (that is, rapeseed, olive, canola and other plant oils). Full-fat mayonnaise will be replaced with low-fat mayonnaise in sandwiches and other lunch options.

No sauces or accompaniments will be added to any meal unless the employee requests it. Chips and French fries will be removed from the menus two days a week and replaced with different potato options, for example baked potatoes. Pizzas will be removed from the menus three days a week. All desserts will be fruit-based. Soft carbonated drinks will be restricted and replaced with water, milk and unsweetened fruit juice options.

To increase fibre, fruit and vegetables, white pasta, rice and bread will be replaced with wholegrain alternatives. Fruit and vegetables will be added to rice, pasta, soup and meat dishes. A buffet-style fresh salad bar will be available to accompany any dish daily. Fresh whole fruit will be available throughout the day.

Portions of whole fruit will be offered at discount prices.

To introduce portion size control, workplaces will be recommended to comply with the FSAI guidance on portion size [23]. Training will be provided to all catering staff regarding strict portion size control. Standard serving tools will be used by caterers and employees to control portion size at mealtimes.

Healthier alternatives will be strategically positioned: healthy snacks, such as whole fresh fruit, dried fruit, nuts without chocolate, salt or sugar, brown sandwiches, brown soda bread and seeds will be positioned at eye level at the entrance of the canteen and in the vending machines. Chocolate, sweets, biscuits and crisps will be restricted and replaced where possible with healthy snacks in the canteen and in the vending machines located in the canteen. Full-size chocolate bars will be replaced with smaller options. Salt will be removed from the tables and will be replaced with sachets.

### Feasibility and piloting

The second phase includes (1) testing procedures, (2) estimating recruitment and (3) determining an appropriate sample size.

#### Testing procedures

In 2009, we carried out a cross-sectional comparison pilot study in two public hospitals in Cork, Ireland; one of which had implemented a long-term (2 years) catering intervention designed to reduce dietary fat, saturated fat, sugar and salt intake. All menus were modified. High-salt products (gravy mixes, stock cubes) and processed meat (bacon, corned beef) were replaced with low-salt options (turkey, chicken and fish). Fresh herbs, spices and garlic were introduced. Salt was removed in cooking. Saltcellars were removed from the tables in the canteen but small salt sachets were available at the service counter. Nutrition information was displayed in the canteen area. No sauces were added to any meals without the employee’s consent. All desserts were fruit-based. Staff members were encouraged to consume extra salad and vegetable options at no extra cost. Cooking methods with oil were reduced. No catering changes were implemented in the second hospital.

A total sample of 100 random employees aged 18 to 64 years (50 from each hospital) who consumed at least one main meal in the hospital staff canteen daily took part in the study. Dietary intakes and sociodemographic characteristics were assessed. Reported mean intakes of total sugars, total fat, saturated fat and salt were significantly lower in the intervention hospital when adjusting for age and sex. Estimated average salt intake in the intervention hospital (5.6 g/day) did not exceed the tolerable upper limit of 6 g/day vs. a mean salt intake of 6.7 g/day in the non-intervention hospital.

The study findings, published in the journal Public Health Nutrition [24], suggest that a structured catering initiative sustained over a relatively long period may influence long-term positive food choices at work and at home. Although these findings should be interpreted cautiously given the small sample size, many of the proposed dietary environmental modification and nutrition education components of the 'Food Choice at Work’ study have been shown to be acceptable and feasible in a workplace setting.

#### Estimating recruitment

A four week period in each workplace will be allocated to estimate recruitment. The time taken to schedule employees and conduct baseline data collection appointments will be recorded to inform the other stages of data collection.

#### Determination of sample size

A decrease in BMI by 1 kg/m^2^ (1 unit) and a 2 g average fall in dietary salt intake would have population health significance and clinical significance in terms of the risk of diet-related disease, for example, hypertension. To detect this difference in BMI between the control and intervention groups at follow-up session after 7 to 9 and 13 to 16 months and assuming a common standard deviation of 3.77, it is estimated that a sample size of 448 (112 per workplace) would have 80% power at the 5% significance level (findings from a previous study show that a 1 kg/m^2^ difference was independently associated with 13% higher risk for hypertension) [25,26]. The study will also be adequately powered (80% power at the 5% significance level) to detect a fall in dietary salt intake between the control and intervention groups at follow-up periods of 7 to 9 and 13 to 16 months using a standard deviation of 4.2 (In a previous intervention study the response within each participant group was normally distributed with standard deviation 4.2) [27].

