**Methods/design:**

A clustered controlled trial involving four large multinational manufacturing workplaces in Cork will be conducted. The complex intervention design has been developed using the Medical Research Council’s framework and the National Institute for Health and Clinical Excellence (NICE) guidelines and will be reported using the TREND statement for the transparent reporting of evaluations with non-randomized designs. It will draw on a soft paternalistic “nudge” theoretical perspective. Nutrition education will include three elements: group presentations, individual nutrition consultations and detailed nutrition information. Environmental dietary modification will consist of five elements: (a) restriction of fat, saturated fat, sugar and salt, (b) increase in fibre, fruit and vegetables, (c) price discounts for whole fresh fruit, (d) strategic positioning of healthier alternatives and (e) portion size control. No intervention will be offered in workplace A (control). Workplace B will receive nutrition education. Workplace C will receive nutrition education and environmental dietary modification. Workplace D will receive environmental dietary modification alone. A total of 448 participants aged 18 to 64 years will be selected randomly. All permanent, full-time employees, purchasing at least one main meal in the workplace daily, will be eligible. Changes in dietary behaviours, nutrition knowledge, health status with measurements obtained at baseline and at intervals of 3 to 4 months, 7 to 9 months and 13 to 16 months will be recorded. A process evaluation and cost-effectiveness economic evaluation will be undertaken.

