##### Study duration

The total study duration is 16 months, with the interventions being delivered over a 9-month period. Follow-up is for 6 months post-intervention.

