### Limitations

The study design is not randomized. However, the characteristics of each workplace are similar, including work schedules (shift patterns), company type (production and office based), skilled and educated workforces. Demographic information from the questionnaires will determine further comparison between worksites. The sample will also be randomly selected from the employee lists.

There is no concealment of allocation. The workplaces were purposively selected to ensure that all components of the interventions could be implemented successfully.

There is a lack of blinding: given the nature of the workplace interventions (nutrition consultations or environmental change), it is not possible to adequately blind personnel or participants. Participants will be masked to the study hypothesis.

There is a selection bias: healthy employees may be more likely to participate but demographic variables of non-responders will be examined to ensure the participants are representative of the general workforce.

Recall bias and social desirability bias may be evident, given that both dietary measurements (FFQ and 24-hour dietary recall) are self-reported. Dietary data may be overestimated or underestimated. The FFQ will be completed by the participant without the presence of the researcher. The 24-hour dietary recall method is clearly structured with specific food prompts so recall bias may be prevented. The researcher will start each visit with the 24-hour dietary recall and will not comment about food before the recall so social desirability bias may be reduced.

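### The 80% BMI power stated for the 13 to 16 month visit rests on 448 measured participants, the same 448 taken in, and so leaves no margin for loss

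*Protocol article*

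**What the plan says.** The section Determination of sample size takes a BMI difference of 1 kg/m² between control and intervention groups at the 7 to 9 and 13 to 16 month follow-ups, "assuming a common standard deviation of 3.77", and concludes that "it is estimated that a sample size of 448 (112 per workplace) would have 80% power at the 5% significance level". The abstract (Methods/design) gives the same figure as the intake: "A total of 448 participants aged 18 to 64 years will be selected randomly". Under Study duration, "The total study duration is 16 months, with the interventions being delivered over a 9-month period". The section Long-term follow-up relies on the last visit to judge whether dietary change is sustained. The inclusion criteria require employees to be contracted for the study period. The article states no expected loss to follow-up and no inflation of the sample size.

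**The concern.** A power calculation for a comparison at a given visit returns the number of people who must be measured at that visit. If the same number is recruited, the stated power holds only if everyone recruited is measured. Here the visit is 13 to 16 months after baseline, and attendance depends on people staying employed on site, staying willing and keeping the appointment. The contract criterion limits turnover but does not rule out resignation, withdrawal or missed visits.

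At stake is the reading of a null BMI result at the last visit. It would be judged against 80% power for a 1 kg/m² difference, although that power belongs to a complete-follow-up scenario.

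**Working it through.** **Inputs**, all from Determination of sample size unless noted:

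- difference δ = 1 kg/m²
- common SD σ = 3.77
- power 80%, significance level 5%, sidedness not stated
- total 448, 112 per workplace
- one control workplace, A (abstract; Modelling process and outcomes)
- loss rate not given, so a range is assumed.

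**Step 1: reproduce 448.** For two equal groups and a two-sided test, n per group = 2(1.960 + 0.842)² σ²/δ² = 2 × 7.849 × 14.213 = 223.1, rounded up to 224, so 2 × 224 = 448. Solving with the t distribution gives 224.07 per group. Other readings do not return 448:

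- one-sided, equal groups: 352
- two-sided, 1:3: 596
- one-sided, 1:3: 472

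So 448 matches the two-sided, equal-group requirement with zero allowance for loss.

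**Step 2: power on that same basis under assumed loss.** Power ≈ Φ[δ/(σ√(1/n₁ + 1/n₂)) − 1.960], with each group multiplied by (1 − loss). With 224 v 224 and no loss, 1/(3.77 × 0.09449) = 2.807 and Φ(0.847) = 80.2% (79.99% by the t-test). Loss multiplies the 2.807 by √(1 − loss):

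| Assumed loss | Power, 224 v 224 at entry |
|---|---|
| 0% | 80.2% |
| 5% | 78.1% |
| 10% | 75.9% |
| 20% | 70.9% |
| 30% | 65.1% |

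The t-test values are within 0.3 points of these.

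**Step 3: the comparison the design contains.** Only workplace A is a control, so control versus intervention is 112 v 336 if the three intervention workplaces are pooled, or 112 v 112 for one workplace against control. For 112 v 336, √(1/112 + 1/336) = 0.10911, 1/(3.77 × 0.10911) = 2.431 and Φ(0.471) = 68.1%. The difference detectable with 80% power is (1.960 + 0.842) × 3.77 × 0.10911 = 1.15 kg/m², divided by √(1 − loss) when there is loss:

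| Assumed loss | Power, 112 v 336 | Detectable difference, 112 v 336 (kg/m²) | Power, 112 v 112 |
|---|---|---|---|
| 0% | 68.1% | 1.15 | 51.0% |
| 10% | 63.6% | 1.21 | 46.9% |
| 20% | 58.5% | 1.29 | 42.7% |
| 30% | 53.0% | 1.38 | 38.2% |

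All figures are unadjusted for baseline and make no allowance for clustering by workplace.

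**Step 4: salt.** With the 2 g fall named in the section and SD 4.2, the same formula needs 70 per group. Even on the smallest pairing, 112 v 112, power is about 95% with no loss, 89% at 20% and 84% at 30% (the last by the t-test). Before clustering, loss at these rates does not threaten the salt claim.

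**The case against.** **This is only silence in a condensed article.** A journal article may leave attrition to the full protocol. That would answer a complaint that loss is not mentioned. It does not answer this point, because the article prints a power, a sample size and the inputs, and those inputs yield 448 with no allowance. A one-sided, equal-group calculation needs 352 and would leave room for 1 − 352/448 = 21% loss. But the article states neither a one-sided test nor such an allowance, and the two-sided calculation matches exactly.

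**The calculation is not the analysis.** This stands in part. The article plans to analyse change, with four waves and a mixed effects model, whereas the calculation is a plain comparison of means at one time. Baseline adjustment multiplies the variance by 1 − ρ², with ρ the correlation between baseline and follow-up BMI, so it offsets a loss d when ρ² ≥ d: ρ of about 0.45 for 20% and 0.55 for 30%. The documents give no ρ. A reader might infer that the trial cannot reach 80% power once anyone is lost. The documents do not support that. They show only that the stated calculation has no margin.

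**The loss is hypothetical and small losses cost little.** Also fair. Losing two people moves the normal-formula power from 80.2% to 79.98%, which has no practical meaning, and 5% loss costs about 2 points.

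**Loss is secondary to the choice of comparison.** True in size: 112 v 336 is at 68% before anyone is lost. This is why corrected figures should not be given on the 224 v 224 basis. It does not remove the point, since settling the comparison alone would still leave no allowance for loss.

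**Refusals.** A reader might infer that the shortfall begins at baseline, because 448 are to be selected and the Limitations section says that "healthy employees may be more likely to participate but demographic variables of non-responders will be examined". That does not follow. The 448 are called participants and can be read as those enrolled, with non-responders additional to them. How refusals are replaced is a detail that a full protocol would normally hold.

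**Conclusion.** The point holds in a limited form. The 448 is, to the participant, the uninflated two-sided requirement for two groups of 224, and the abstract uses it as the intake. The 80% stated for 13 to 16 months is therefore a complete-follow-up figure. On the article's own two-group basis the cost is about 2 points at 5% loss, 4 at 10%, 9 at 20% and 15 at 30%, so it is material from about 10%. The loss rates are assumptions, and the figures are for an unadjusted comparison before clustering.

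It would be wrong to conclude that 448 is simply the number needed at the last visit. That holds only for 224 v 224, and the design has one control workplace of 112. The point concerns the BMI claim only.

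**What to change.** Keep 448. In Determination of sample size, replace the flat 80% for BMI with power and detectable difference at an explicit assumed loss, computed for the comparison to be made with workplace A as the only control. If that is A against the three intervention workplaces pooled, the 112 v 336 columns above apply. If it is A against one workplace, the 112 v 112 column applies. State that the figures are unadjusted and precede any allowance for clustering, and that baseline adjustment may recover some power. Do not describe 448 as the number needed at follow-up. The salt statement needs no change on this account.

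The cost is a few sentences and a less favourable stated power, with no added participants and no change to design or analysis.

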#### Modelling process and outcomes

This behavioural complex intervention design is guided by the detailed principles and recommendations of the NICE guidelines [1]. The study focuses on two potential methods to improve long-term dietary behaviour in the workplace including environmental dietary modification and nutrition education. Both methods will be measured independently and collectively in purposively selected workplaces. Workplace A (the control) will continue to follow usual practice. No changes will be implemented. Workplace B will receive nutrition education. Workplace C will receive nutrition education and environmental dietary modification. Workplace D will receive environmental dietary modification alone. The intervention design has been developed by the research team (nutritionists, dieticians, public health and health promotion researchers), catering stakeholders in Ireland (representatives of the Catering Managers Association of Ireland), workplace stakeholders (catering managers, human resources managers, occupational health managers) and the target population, that is manufacturing employees. Figure 2 illustrates the trial design.

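### The stated 80% power for a 1 kg/m² BMI difference between control and intervention does not follow from 112 participants per workplace; on the printed inputs it is about 51% per pairwise comparison

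*Protocol article*

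**What the plan says.** All the inputs stand in the protocol article under Determination of sample size. The targets are "A decrease in BMI by 1 kg/m^2^ (1 unit) and a 2 g average fall in dietary salt intake". The BMI calculation is framed as a difference between groups: "To detect this difference in BMI between the control and intervention groups at follow-up session after 7 to 9 and 13 to 16 months", "assuming a common standard deviation of 3.77". The result is "it is estimated that a sample size of 448 (112 per workplace) would have 80% power at the 5% significance level".

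The design has four arms of one workplace each. The abstract says "No intervention will be offered in workplace A (control). Workplace B will receive nutrition education", and the section Modelling process and outcomes adds "Workplace C will receive nutrition education and environmental dietary modification. Workplace D will receive environmental dietary modification alone". The Study hypothesis section expects the combined programme to do better than education alone and than environmental modification alone, that is, C against B and C against D. The Statistical analysis section compares workplaces A, B, C and D and describes no pooling of the intervention workplaces.

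**The concern.** The control arm is one workplace with 112 people, and so is each intervention arm. A comparison of control with any one intervention, or of the combined arm with either single-component arm, is therefore 112 v 112. The printed difference, SD and power call for twice that number per group.

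BMI change is one of the primary health-status outcomes, and the 448 is derived from the BMI target. If the 80% figure is carried into the results paper, a null BMI finding in B, C or D would be read as an adequately powered negative. On the plan's own figures, an unadjusted comparison of follow-up BMI would miss a true 1 kg/m² difference about half the time.

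**Working it through.** **Inputs (all from Determination of sample size).** Difference δ = 1 kg/m²; SD σ = 3.77; significance 5%; power 80%; 448 in total, 112 per workplace. The article does not say whether the test is one- or two-sided; I take two-sided as the usual default.

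**Reproducing 448.** The two-sample formula is n per group = 2(z₀.₉₇₅ + z₀.₈₀)²σ²/δ².

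- (1.960 + 0.842)² = 7.849 and 3.77² = 14.213.
- n = 2 × 7.849 × 14.213 = 223.1, so 224 per group.
- Two groups: 2 × 224 = 448, the printed total.
- Check: 224 v 224 gives 80.0% power (noncentral t).

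A second route reaches the same figures. The one-sample formula drops the factor 2 and gives 7.849 × 14.213 = 111.6, so 112 per workplace and 4 × 112 = 448. The document does not show which route was taken.

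**Power at the printed allocation.** SE = σ√(1/n₁ + 1/n₂). Power is from the noncentral t, two-sided 5%.

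| Comparison | n₁ v n₂ | SE | δ/SE | Power |
|---|---|---|---|---|
| Any two workplaces | 112 v 112 | 0.504 | 1.98 | 50.7% |
| Control v three interventions pooled | 112 v 336 | 0.411 | 2.43 | 67.9% |
| Two workplaces v two workplaces | 224 v 224 | 0.356 | 2.81 | 80.0% |

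The normal approximation gives 51.0%, 68.1% and 80.2%.

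**Detectable difference at 112 v 112 with 80% power.** 2.802 × 3.77 × √(2/112) = 1.41 kg/m².

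**Salt, for comparison.** With δ = 2 g and σ = 4.2, SE = 4.2 × √(2/112) = 0.561, δ/SE = 3.56 and power is about 94% at 112 v 112. The salt claim survives this check.

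**If change from baseline were analysed.** The SD of change is 3.77 × √(2(1 − r)), where r is the baseline–follow-up correlation. The article gives no r, so these values are assumptions, and they hold only if 3.77 is the between-person SD of BMI at one time point.

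| Assumed r | SD of change | Power, 112 v 112 |
|---|---|---|
| 0.70 | 2.92 | 0.72 |
| 0.75 | 2.67 | 0.80 |
| 0.80 | 2.38 | 0.88 |

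Every power figure here treats participants as independent. The Unit of analysis section says standard errors will be adjusted for clustering within the four workplaces. That adjustment can only reduce these values.

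**The case against.** Four arguments can be made for the plan.

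- **The 2×2 layout.** A gets neither component, B education, D environmental change and C both. Each component's margin (B and C v A and D; C and D v A and B) is 224 v 224 and has 80% power. The statement "Both methods will be measured independently and collectively in purposively selected workplaces" is about methods and is compatible with such a marginal analysis. It stands that the design contains these contrasts. They are not, however, the comparison for which power is claimed, which is "To detect this difference in BMI between the control and intervention groups", and they do not test C against B or C against D.
- **Pooling or one-sided testing.** A one-sided test gives 63.3% at 112 v 112. A one-sided test of control against all three interventions pooled comes nearest, at 78.4%. That is still short of 80%, and neither device is described.
- **Within-workplace origin.** The one-sample formula reproduces 112 exactly, and the section opens by speaking of a decrease in BMI. A reader might infer that 448 is certainly a two-group total wrongly divided by four; the document cannot settle that. It matters little, because the text states a between-group comparison and 112 per arm falls short under either origin.
- **Use of baseline data.** The outcome is defined as change in BMI, and repeated-measures and mixed models are planned. A reader might infer that the eventual BMI analysis is bound to have only 51% power. The documents do not support that: a longitudinal analysis could do better if r is high. The power paragraph, however, neither invokes this nor gives a correlation, so it cannot support the printed claim.

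Two further inferences should be resisted. The whole trial is not shown to be underpowered at the individual level, since salt is not affected. Nor does the lack of a stated attrition allowance count against the plan: an article commonly leaves that to the full protocol, and it does not say whether 448 is the number recruited or the number analysed.

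**Conclusion.** The concern holds in this limited form: the 80% power claim for BMI is inconsistent with the difference, SD and group sizes printed beside it. Power is about 51% for each pairwise comparison of workplaces and about 68% for control against all interventions pooled. At 112 per workplace the difference detectable with 80% power is 1.41 kg/m², not 1.

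This rests on a two-sided 5% test of follow-up means, on 3.77 being the SD that applies to the compared quantity, and on no allowance for clustering. The size of the clustering loss cannot be computed from the document, which gives no intraclass correlation. How 448 was obtained remains an inference, and the conclusion does not depend on it. Because the error lies in the stated power for the variable behind the sample size, and rewording corrects it, it should be fixed.

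**What to change.** Rewrite the BMI sentence under Determination of sample size. State the comparison it refers to and that the test is two-sided. Say that 112 participants per workplace give about 51% power for a 1 kg/m² difference in follow-up BMI in each pairwise comparison (detectable difference 1.41 kg/m² at 80% power), before clustering. Remove the 80% claim for BMI. On this point the salt sentence can stay, with the note that its roughly 94% is also before clustering.

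If the authors prefer to justify 112 per workplace on change from baseline or baseline-adjusted BMI, they should:

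- state the baseline–follow-up correlation and its source;
- show a range, for example the assumed r of 0.70, 0.75 and 0.80, giving change-score power of about 0.72, 0.80 and 0.88 before clustering;
- confirm that 3.77 is not already a change SD, in which case this route does not help;
- carry the clustering caveat into the same sentence, so that one unsupported figure is not replaced by another.

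The cost is wording only. No extra participants are needed, but the headline BMI power becomes less favourable unless the baseline-based justification can be supported.
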